### Planned statistical analyses by aim

#### Conceptual model

The statistical analysis plan is guided by our conceptual model linking neighborhood-level characteristics including PM_2.5_ exposure, social isolation, and cognitive function/ADRD risk in Fig 5.

**Fig 5 pone.0312660.g005:**
[figure not shown]
Conceptual model.

#### Aim 1A

General linear mixed model (GLMM) analyses with year and season nested in participants within neighborhood block groups will be conducted for Aim 1A to evaluate the effects of changes in PM_2.5_ averaged over burn and non-burn seasons, as well as other temporal integration windows, on CF and SI. Controlling for random variance in outcomes across neighborhood block groups protects against inflated Type I errors due to neighborhood-level intraclass correlations. Additionally, linear and curvilinear trajectories for CF/ADRD risk and SI over the 3-year period associated with PM_2.5_ levels will be assessed using multilevel linear growth modeling. Both time-varying (e.g., health behaviors, work and home environments, comorbidities) and time-invariant (e.g., sex) individual- and neighborhood-level covariates (see Fig 1) will be incorporated into prediction models to control for these additional individual and neighborhood/community influences on the outcomes.

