All PurpleAir data from study-specific monitors are available for download through the PurpleAir Data Download Tool. Though there are not extensive publicly operating PurpleAir monitors in the study area, there are several PurpleAir monitors that operate east of the study area closer to the Atlantic coast, which in prior study campaigns (Sablan *et al*. 2024) [44] have been used to compare to data collected as part of our study. As of 2023, PurpleAir charges for data download for publicly operating monitors using a point-based billing system. Points range in value (100,000 to 1,000,000 per USD) depending on how many are purchased. The cost of data on a point basis depends on the data fields and number of observations requested. Based on prior work, the research team will leverage recently developed high-resolution fire-detection and Aerosol Optical Depth (AOD) products from NASA’s Moderate Resolution Imaging Radiospectrometer (MODIS), NOAA’s Visible Infrared Imaging Radiometer Suite (VIIRS), and the Geostationary Operational Environmental Satellite (GOES-16) to develop local climatologies of fire and smoke. This procedure leverages NOAA’s Hazard Mapping System (HMS) satellite-based observations to separate smoke from non-smoke influence. We will create daily kriged surfaces of bias-corrected PM_2.5_ for each study community for baseline and subsequent study years. Participants will be assigned exposures based on their home location. Based on daily estimates of PM_2.5_, we can aggregate the observations at any temporal resolution, including hour, day, week, month, and burn and non-burn seasons, to form the exposure assessment strategy for Aim 1.

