### Sample size/power

#### Sample size calculations for full sample

Sample size estimates were made to attain .8 power for Aims 1 and 2. The intraclass correlation was assumed to be .05 based on the cluster of neighborhoods within rural communities. For Aim 1a, an assumed effect size of *d* = .35 of the effect of PM_2.5_ on ADRD risk across burn seasons during the 3-year period was based on prior studies of cognitive decline and all-cause dementia in women related to PM_2.5_ [63]. Assuming 20 persons sampled per PM_2.5_ monitor area, this resulted in monitors covering 7 neighborhood block groups per community or N = 660 stratified across the 5 communities. For Aim 1b, effect size estimates for racial differences were based on findings of an approximately a twofold difference in hazard ratios of incident AD based on PM_2.5_ for non-Hispanic Black women compared to non-Hispanic White women or a difference in Cohen’s *d* = .45 [64] Assuming 20 persons sampled per PM_2.5_ monitor area, sample size estimates for power = .8 for the interaction of burn season by race, resulted in monitors covering at least 10 neighborhood block groups in each community for a total sample size of N = 1,000 stratified across the five communities. For Aim 2a, an assumed effect size of the built environment on cognitive function of *d* = .325 was based on Besser’s study finding of the relationship of proportion retail in 1/2-mile buffer to digit symbol coding as a measure of processing speed [65]. Assuming 20 persons sampled per neighborhood (census block), the sample size to detect an effect of the built environment on ADRD risk required six block groups per community for a total sample size of N = 600 stratified across five communities. Because Aim 1b provides the limiting sample size, the target sample size will be 1,000. Although there is a lack of literature to base the effect size for Aim 2b, the minimally detectable effect size with number of neighborhood block groups equal to 10 and n = 20 is *d* = .38. To account for 8% attrition [66–68], 1,087 participants will be recruited for the study. Conversions among risk measures and Cohen’s d were made in accordance with prior research and assumed a base rate = 0.107 of all-cause dementia [69]. Power analysis programs for mixed linear models, GLIMMPSE [70] CRT Shiny App [71] and PowerUp! [72] were used in these calculations.

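### Aim 1A credits the block-group random effect with Type I error protection that covers only time-constant neighborhood correlation, while the PM2.5 exposure it tests varies by place and season

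*Protocol article*

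**What the plan says.** The Aim 1A paragraph of the planned analyses specifies a general linear mixed model with "year and season nested in participants within neighborhood block groups", used "to evaluate the effects of changes in PM_2.5_ averaged over burn and non-burn seasons" and over other time windows. It then gives the reason for the block-group level: "Controlling for random variance in outcomes across neighborhood block groups protects against inflated Type I errors due to neighborhood-level intraclass correlations". Growth models and time-varying individual and neighborhood covariates are added. Aim 1B builds on the same model.

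Under Air pollution data the exposure is defined in two steps: "We will create daily kriged surfaces of bias-corrected PM_2.5_ for each study community for baseline and subsequent study years", and "Participants will be assigned exposures based on their home location".

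The full-sample size section gives one clustering figure: "The intraclass correlation was assumed to be .05 based on the cluster of neighborhoods within rural communities". It does not say how much of that correlation persists from one season to the next. No place-by-season random effect and no cluster-robust variance appears in the article.

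**The concern.** PM2.5 averaged over a season and assigned by address from a community surface will be nearly the same for neighbors in that season, and will differ in the next. The coefficient therefore draws largely on comparisons between seasons within a place. A block-group effect that does not change over time drops out of those comparisons, so it cannot absorb anything that lifts or lowers the outcome for a whole neighborhood in one season only. Examples would be a local outbreak, a closed meeting place or a change of assessor. These are illustrations, not events the article reports.

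Under the stated nesting, such shared variation is treated as independent personal noise. The standard error of the PM2.5 effect is then too small, and a chance local event can be reported as an effect of smoke on isolation or cognition. A fixed calendar-season term would not cure this, because it removes only what all places share.

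**Working it through.** **Design figures from the article.** 20 persons per block group, 10 block groups per community, 5 communities: 10 × 20 × 5 = 1,000. With 8% attrition, 1,000 / (1 − 0.08) = 1,087, which reproduces the recruitment target. ICC = .05. Cognition and isolation are scheduled at T1 to T6, so there are 6 outcome occasions.

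**Assumptions not in the article.** Two-sided α = .05; residual share of total variance .45; PM2.5 effectively equal within a block group in a season; everyone in a place assessed in the same six seasons.

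**Formula.** Let m be the number of persons sharing a place-season shock and r the shock variance divided by the residual variance. For the within-place PM2.5 slope, true variance / modelled variance = 1 + m·r, and actual error = 2 × [1 − Φ(1.96 / √(1 + m·r))].

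**Worked case.** Block-group-by-season variance 1% of total: r = .01 / .45 = .0222; 1 + 20 × .0222 = 1.444; √1.444 = 1.202; 1.96 / 1.202 = 1.631; error ≈ .10. The error doubles at m·r ≈ .42, so r ≈ .021 for m = 20. That is .021 × .45 ≈ 1% of total variance (0.6% to 1.3% for a residual share of .3 to .6).

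**Simulation.** REML fit with participant and block-group random intercepts, no true PM2.5 effect, ICC .05, 600 runs per setting (Monte Carlo standard error about .01 to .02). Ranges cover models with and without fixed visit effects.

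| Block-group-by-season share of total variance | Formula | Simulated error |
|---|---|---|
| 0 | .05 | .04–.05 |
| 0.5% | .08 | .07 |
| 1% | .10 | .08–.09 |
| 2.5% | .18 | .17–.19 |

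Fixed visit effects did not remove the inflation.

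**Community-wide shocks.** In the same simulation, with PM2.5 variation mostly shared within communities (an assumption), the error was .09 at 0.1% of total variance, .14–.15 at 0.25% and .30–.33 at 1%.

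**Does the remedy work?** With a block-group-by-season random effect added, the error returned to .04–.06 for block-group-level shocks. For community-wide shocks of 1% it stayed at about .23–.24. In a separate simulation, a community-by-season effect with a t reference on (5 − 1) × (6 − 1) − 1 = 19 degrees of freedom gave .04–.05. The two terms were not tested together.

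**Aim 1a power.** The article needs N = 660 for .8 power in Aim 1a (noncentrality 2.80) but targets 1,000 because Aim 1b is limiting. Take an ICC of .05, a residual share of .40 and a between-season correlation of the neighborhood effect of .8. The shock variance is .05 × .2 = .01. The standard-error ratio is √[(.01 + .40/20) / ((.40 + .01)/20)] = √(.030 / .0205) = 1.21. Power at N = 1,000 is Φ(2.80 × √(1000/660) / 1.21 − 1.96) = Φ(0.89) = .81. At a correlation of .9 the ratio is 1.11 and power .87. At .5 the ratio is 1.455 and power .66.

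**The case against.** Four points on the other side have weight.

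- The sentence is qualified. It speaks of inflation due to neighborhood-level correlation, and for correlation that is constant over time it is right. This stands, and the simulation with no place-by-season variance confirms it.
- The article is condensed, does not call the block-group effect a constant intercept, and may leave the full list of random effects to an analysis plan that is not shown. It also plans time-varying and neighborhood covariates that could absorb part of any local seasonal variation. This lowers the certainty. It does not remove the point, because the article itself states a nesting with season inside the participant and names the block-group effect as the protection.
- Visits run at six-month intervals from each person's own baseline, so neighbors can be assessed months apart within one season. A short local event need not reach all of them. The simulated design is more synchronized than the study, and the true inflation may be smaller.
- The introduction describes steep gradients in smoke plumes in space and time, and the sensor network is justified by plume variability. How much seasonal PM2.5 is common to a whole community is therefore unknown.

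A reader might infer that the test must run at twice its nominal error or more. The documents do not support that. They give no place-by-season variance, and the error does not double when the between-season correlation is .9 and shocks are confined to block groups (about .08 to .09). The much larger values need community-wide shocks, for which the article gives no figure. Its ICC concerns neighborhoods.

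A reader might also infer that Aim 1a power falls to about 64%. That ignores the margin between the 660 needed and the 1,000 targeted.

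**Conclusion.** The point holds in a limited form. The stated protection covers time-constant neighborhood correlation and does not extend to variation shared by place and season, which is the level at which the Aim 1A exposure varies. The size depends on a variance the documents do not give: about .07 to .19 for a nominal .05 test if 0.5% to 2.5% of total variance is block-group-by-season, and about .05 if there is none. These shares are small beside the plan's own ICC of .05; 1% is one fifth of it. Community-wide shocks would add to the inflation, and staggered visits may reduce it.

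The figures apply to the Aim 1A main effect. In Aim 1B, shocks common to all groups in a place partly cancel from the race interaction, so the case there is weaker. Aim 1a power stays near .8 or above at between-season correlations of .8 to .9 and falls clearly below only for much lower values.

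**What to change.** In the Aim 1A model, carried into Aim 1B:

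1. Include a random effect for block group by season-year.
2. Assess a community-by-season-year random effect as well, or report it as a sensitivity analysis, since there are only five communities and its variance will be poorly estimated.
3. Use small-sample degrees of freedom (Kenward-Roger or Satterthwaite).
4. Reword the Type I error sentence so that it claims protection only for neighborhood correlation that is constant over time.

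If the full analysis plan already holds these terms, only the sentence needs correcting. The change costs wording and one or two variance components, with no new data or participants. The downside is somewhat wider intervals for the PM2.5 effect.

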#### Aim 1B

Building on the analyses of Aim 1A, GLMM will be employed in Aim 1B to examine effect modification of Aim 1A (i.e., the differential effect of race/ethnicity on the effect of PM_2.5_ on CF and SI) through cross-level interactions of participant race/ethnicity, as well as CF and SI changes over burn season and year, controlling for neighborhood and covariate effects, as determined in Aim 1A.

#### Aim 2A

General linear mixed model analyses of participants nested within neighborhoods (i.e., census block groups) will be used to examine the effect of built and social environments on CF and SI for Aim 2A. Primary analysis will model effects of the four domains of social and built environment and the HNI on baseline CF and SI and on changes over 36 months, accounting for random neighborhood-level variance. Both time-varying (e.g., health behaviors, work and home environments, comorbidities) and time-invariant (e.g., sex) individual- and neighborhood-level covariates (see Fig 1) will be incorporated into prediction models to control for these additional individual and neighborhood/community influences on outcomes.

#### Aim 2B

Building on the analyses for Aim 2A, GLMM will be employed in Aim 2B to examine effect modification of Aim 2A (i.e., the differential effect of race/ethnicity on the effects of built and social environments on CF/ADRD risk and SI) by estimating cross-level interactions of race/ethnicity and built and social environments on the outcomes, controlling for neighborhood and covariate effects, as determined in Aim 2A.

#### Aims 3A and 3B

Random forests, convolutional neural networks, and gradient-boosted models will predict clinical measures and will be evaluated using leave-one-subject-out validation. Performance will be compared with mean and median baseline predictions for statistical significance. The primary analysis will model effects of activity level, social activity, and built environment averaged over burn season and year, although changes over time will also be assessed. Based on a continuous collection of over 8 weeks from 120 participants, we will collect at least 1.5 billion movement readings, 625,000 locations, 43,000 EMA responses, and 3,000 n-back scores. We will use the EMA responses, n-back scores, and ADRD risk scores as our target variables. The independent variables used to form the machine learning feature vectors will be daily digital behavior markers for each participant.

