#### Specific aims

Aim 1. Examine the contribution of particulate matter <2.5μm (PM_2.5_) exposures to social isolation and cognitive function (CF), through multilevel growth modeling.

Aim 1a. Examine baseline levels and growth trajectories of SI and CF associated with changes in PM_2.5_ during agricultural burn and non-burn seasons over a 36-month period, accounting for individual- and neighborhood- level characteristics.Aim 1b. Examine the effect modification of race/ethnicity on the relationship of PM_2.5_ on baseline levels and growth trajectories of SI and CF, accounting for individual- and neighborhood-level characteristics.

Aim 2. Determine the effects of the built environment (e.g., retail destinations, park space) and social environment (e.g., crime, SES) on SI and CF through linear mixed modeling.

Aim 2a. Examine SI and CF associated with the built and social environment over a 36-month period (baseline, and FY 1,2,3), controlling for individual- and other neighborhood-level characteristics.Aim 2b. Explore the effect modification of race/ethnicity on the relationship of the built and social environment with SI and CF, in view of their educational and social disadvantage.

Aim 3. Contextualize SI and CF among residents from different ethnoracial groups using EMA and sensor- derived behavior models during burn and non-burn seasons in a subsample of 120 ethnoracially diverse participants, stratified by Lake O communities.

Aim 3a. Examine residents’ momentary changes in behavioral markers, mood, and cognitive performance, associated with changes in air quality and the social and built environment.Aim 3b. Characterize differences among ethnoracial groups and between women and men in their momentary changes in behavioral markers, mood, and CF performance in response to changes in air quality and the social and built environment.

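### Aim 3's primary analysis lists no air-quality effect and puts sensor-derived behavior on the predictor side, although Aims 3a and 3b make behavior an outcome of air quality

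*Protocol article*

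**What the plan says.** Under Specific aims, Aim 3a is to examine "momentary changes in behavioral markers, mood, and cognitive performance, associated with changes in air quality and the social and built environment". Aim 3b asks how ethnoracial groups, and women and men, differ in "momentary changes in behavioral markers, mood, and CF performance in response to changes in air quality" and in the social and built environment.

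The analysis section headed Aims 3A and 3B describes random forests, convolutional neural networks and gradient-boosted models that predict clinical measures. They are validated by leaving one subject out and compared with mean and median predictions. It then says: "The primary analysis will model effects of activity level, social activity, and built environment", taken as averages over the burn season and the year, and adds "although changes over time will also be assessed". The dependent variables are named: "We will use the EMA responses, n-back scores, and ADRD risk scores as our target variables". So are the inputs: "The independent variables used to form the machine learning feature vectors will be daily digital behavior markers for each participant".

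Three other places bear on the point:
- The smartwatch data-collection section says that behavior and location data will be synchronized with air-quality and environment data. It lists air quality among the location markers.
- Table 2 shows that the EMA items include self-reported physical activity and time spent with others.
- The subsample sample-size section bases Aim 3 on predicting clinical measures from behavior markers (d = 0.52, N = 120, 99% power).

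**The concern.** An aim phrased as a response to air quality needs air quality as an exposure and the response as an outcome. The stated analysis has activity and social activity as the effects to be modelled and mood, n-back and risk scores as the things predicted. Followed as written, it would report how well behavior predicts mood and test scores. It would not report how activity level, travel or time at frequented places changes when the air worsens.

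Behavioral markers are the first outcome named in Aim 3a, and their response to air quality is what Aim 3b compares between groups. The Discussion presents this momentary response as the sub-study's innovation. The Setting section reports residents' experience that smoke keeps them from outdoor social contact, and objective location and activity data are well suited to test that.

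**Working it through.** No arithmetic decides this point. The check sets the aim beside the analysis and asks which side of the model each variable sits on.

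**1. Exposures.** Aim 3a names three: air quality, social environment, built environment. The primary-analysis sentence names three effects: activity level, social activity, built environment. One of the aim's three exposures (built environment) is carried over. Air quality and the social environment are not. Social activity is a behavior, not the social environment. Burn season appears only as a window for averaging. Air-quality effects among the listed primary effects: 0 of 3.

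**2. Outcomes.** Aim 3a names behavioral markers, mood and cognitive performance. The analysis names three target families: EMA responses, n-back scores and ADRD risk scores. Mood is covered by EMA and cognition by n-back. No activity, travel, location or audio-journal marker is a target. Sensor-derived markers among the target families: 0 of 3.

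**3. Inputs.** The independent variables are the daily digital behavior markers. The aim's first-named outcome is therefore on the predictor side.

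**4. Where air quality can enter.** It is one item in the location group of markers, so it may be part of a feature vector, including when self-reported activity or time with others is the target. The stated evaluation is prediction accuracy in left-out subjects against mean and median predictions. That shows whether the whole feature set predicts. It does not give an air-quality effect with an interval, and it contains no contrast of that effect between ethnoracial groups or between women and men.

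**5. What air quality would be conditioned on.** If activity and social-contact features are in the same input set, any contribution of air quality to mood or n-back is what remains after those features. If smoke acts partly by reducing activity and contact, that part is removed.

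**6. The one Aim 3 power figure.** The stated 99% concerns prediction of clinical measures from behavior markers. Neither the test nor alpha is stated. With two-sided alpha 0.05 assumed:
- one-sample or within-person: 0.52 × √120 − 1.96 = 3.74, power above 0.999;
- two groups of 60: 0.52 × √30 − 1.96 = 0.89, power 0.81;
- correlation, with r = 0.52/√(0.52² + 4) = 0.252: Fisher z 0.257 × √117 − 1.96 = 0.82, power 0.79.

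The 99% is reached only on the within-person reading. On any reading it does not size a response of behavior to air quality.

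**7. Data available.** Two four-week periods are 56 days, so 120 × 56 = 6,720 planned person-days, with air quality and behavior already to be synchronized.

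**The case against.** The strongest reply has four parts.

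- **Behavior is not wholly on the predictor side.** EMA responses are targets, and they include self-reported physical activity and time with others. The protocol's own list of digital markers also includes EMA response values and n-back statistics. This stands. A reader might infer that activity and social activity serve only as explanatory variables, and the documents do not support that. The point is limited to sensor-derived markers.
- **Air quality is not absent from the sub-study.** It is a listed location feature, it is synchronized with the behavior data, and one burn and one non-burn period are scheduled. This stands too, but a possible input to a prediction model is not a stated effect estimate. The remark that changes over time will be assessed is not tied to air quality.
- **The study does estimate a link between smoke and social outcomes.** Aim 1A models PM2.5 on social isolation in the full cohort by mixed model, and Aim 1B adds race/ethnicity. A reader might infer that the link goes unestimated in the whole study, which is wrong. Aim 1 uses visit-level scales, however, and does not supply the momentary, sensor-based response that Aim 3 promises.
- **An article condenses.** Choice of markers, random effects and covariates may fairly be left to the full plan. But this article does name a primary analysis, the targets and the inputs, and these do not match its aim. At the same level of detail, the sections for Aims 1 and 2 state models whose exposures and outcomes follow their aims.

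Prediction was also a deliberate choice, since Aim 3 is sized on it. That is a reason to keep it, but it does not answer Aims 3a and 3b.

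**Conclusion.** The point holds for sensor-derived behavior. The stated primary analysis for Aims 3A and 3B includes no air-quality or social-environment effect, and it uses as predictors the markers that Aim 3a makes outcomes. No model stated in the article estimates how those markers change with air quality, or whether the change differs by ethnoracial group or sex.

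The size is structural: 0 of 3 primary effects concerns air quality, 0 of 3 target families is a sensor-derived marker, and 1 of the aim's 3 exposures reaches the primary list. The conclusion assumes only that the targets and independent variables named in that section are the ones meant. It depends on no assumed variance or correlation. The change should be made before analysis, because the data would support the missing model and the list of candidate markers is long enough for a later choice among them to be selective.

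**What to change.** Add to the Aims 3A and 3B section a within-person mixed model that follows the aim:

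- **Outcomes:** a few daily behavior markers named in advance (for example activity level, distance travelled and time at frequented locations), EMA mood and n-back score.
- **Exposures:** PM2.5 matched in time to the participant's data, or burn versus non-burn period, together with the social- and built-environment measures.
- **Aim 3b:** exposure-by-ethnoracial-group and exposure-by-sex interactions.
- **Adjustment:** do not adjust the total PM2.5 effect for activity or social activity, since these may lie on its pathway.

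The machine-learning prediction can stay beside this model. Which of the two is called primary, and the exact random-effects structure, are for the study team to decide. The subsample sample-size section should say that its 99% refers to clinical prediction.

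The cost is a revised paragraph and one extra set of models on data already planned. No new measurement or recruitment is needed.
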